**Methods:**

A single-center, parallel-group, open-cohort randomized controlled trial is being conducted over 3 years. Ethics approval was obtained for the study. Participants who provide informed consent are randomized into 2 groups: the intervention group receives the cancer navigation intervention and the control group receives the standard of care (the usual medical care offered by health care practitioners). The baseline study time point spanned January to March 2025, the first follow-up spanned April to June 2025 at 3 months after enrollment, and the second follow-up spanned July to September 2025 at the end of 6 months after enrollment. The cancer navigation intervention comprises direct psychosocial and educational webinars, coordinated telephone support services, and community-based cancer care resources. Professional navigators are qualified registered nurses who facilitate information and connect participants with available supportive resources, services, and programs. The main outcomes are financial distress, quality of life, and satisfaction with navigation and interpersonal relationships. The Comprehensive Score for Financial Toxicity–Functional Assessment of Chronic Illness Therapy, Functional Assessment of Cancer Therapy–Breast, Breast Cancer Navigation Survey, Participant Satisfaction With Navigation Scale, Satisfaction With Interpersonal Relationships Survey, and Breast Cancer Navigation Interview are used in the study. Steps are being taken to ensure the trustworthiness of the qualitative data. With a 5% level of significance (2 tailed) and 90% power, the sample size was calculated as 108.

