### Data Measurement Instruments and Outcomes

The main outcomes are financial distress; QOL, such as physical, social, emotional, and functional well-being; and satisfaction with navigation and interpersonal relationships, measured using the instruments outlined in this section.

A sociodemographic survey is used to collect the demographics of the participants.

The COST-FACIT was developed by de Souza et al [36] in conjunction with the University of Chicago and is a patient-reported outcome measure that describes the financial distress experienced by patients with cancer.

The FACT-B is a 37-item instrument designed to measure 5 domains of health-related QOL in patients with breast cancer: physical, social, emotional, and functional well-being and a breast cancer subscale. The FACT-B was developed with an emphasis on patients’ values and brevity [37].

The Breast Cancer Navigation Survey (BCNS) comprises 10 items on a 5-point rating scale from “very dissatisfied” to “very satisfied” and 3 items on a 3-point rating scale from “very dissatisfied” to “very satisfied” [38]. This survey takes 10 minutes to complete (Multimedia Appendix 1).

The Participant Satisfaction With Navigation Scale (PSNS) has 26 items on a 5-point rating scale, from “very satisfied” to “do not know” or “refuse to answer,” was developed by a multidisciplinary team of researchers and clinicians from the National Cancer Institute (NCI)–sponsored Patient Navigation Research Program, led by Jean-Pierre [39]. This survey takes 10 minutes to complete.

The Satisfaction With Interpersonal Relationships Survey comprises 10 items on a 5-point rating scale from “very dissatisfied” to “very satisfied” and 3 items on a 3-point rating scale from “very dissatisfied” to “very satisfied” [40]. This survey takes 10 minutes to complete.

The Breast Cancer Navigation Interview includes 10 questions on perspectives on diagnosis, treatment, and navigation (Multimedia Appendix 2).

Internal consistency reliability for the COST-FACIT for participants diagnosed with breast cancer using Cronbach α for the 2-factor structure was 0.76 to 0.82. A pretest with 30 female patients with breast cancer found a mean COST-FACIT score of 21.23 (SD 9.85). Construct validity for the COST-FACIT score correlated negatively with higher psychological distress and positively with better QOL and lower out-of-pocket costs.

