### Data Analysis

All quantitative data will be analyzed using the intention-to-treat principle. Participants who engaged with the study from October 2025 to December 2025 will be included in the analysis.

The FACT-B is the primary measure used to evaluate the effectiveness of professional navigation on health-related QOL. Changes in FACT-B total scores and the scores on its 5 subscales (physical, social, emotional, and functional well-being and the breast cancer subscale) from baseline (T1) to 3 months (T2) and 6 months (T3) will be compared between the cancer navigation intervention and SOC control groups. A repeated-measure ANOVA will be used to determine the interaction between time and the treatment group. A change of 6 to 7 points on the FACT-B is considered clinically significant for this population.

Financial toxicity is an indicator of socioeconomic distress. Financial burden will be quantified using the COST-FACIT instrument. Descriptive statistics will be generated. To determine the impact of financial toxicity on health-related QOL, ANOVAs will be conducted to assess the associations between COST-FACIT scores and health-related QOL outcomes.

The BCNS analyzes participant satisfaction across 13 items to evaluate the user-friendliness and clarity of the program objectives.

The PSNS uses 26 items to measure overall satisfaction with the navigation process. Higher scores will be correlated with secondary outcomes such as treatment adherence using predictive validity testing.

The Satisfaction With Interpersonal Relationships Survey evaluates soft skills and trust in the professional navigator. Discriminant validity will be assessed by distinguishing between technical competence and interpersonal satisfaction scores.

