### Comprehensive Score for Financial Toxicity–Functional Assessment of Chronic Illness Therapy

Age group (*P*=.05), education level (*P*<.05), employment status (*P*=.01), and place of residence (*P*<.03) were significantly associated with COST-FACIT scores.

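### Financial distress is listed as a main outcome, but the stated COST-FACIT analyses do not include a comparison between the randomised arms

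*Protocol article*

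**What the plan says.** The Abstract (Methods) states: "The main outcomes are financial distress, quality of life, and satisfaction with navigation and interpersonal relationships". The section on instruments and outcomes repeats this: "The main outcomes are financial distress; QOL, such as physical, social, emotional, and functional well-being; and satisfaction with navigation and interpersonal relationships". COST-FACIT is the instrument for the first of these. Table 2 schedules it for the intervention and control groups at baseline and at 6 months, with no 3-month assessment.

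The Data Analysis section says of it: "Financial burden will be quantified using the COST-FACIT instrument", then "Descriptive statistics will be generated". The remaining step has the stated purpose "To determine the impact of financial toxicity on health-related QOL", for which "ANOVAs will be conducted to assess the associations between COST-FACIT scores and health-related QOL outcomes".

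The same section handles FACT-B differently. Changes in its total and subscale scores "will be compared between the cancer navigation intervention and SOC control groups", using a repeated-measures ANOVA aimed at the time-by-group interaction. FACT-B is called the primary measure, and the Sample Size and Power section rests on it alone.

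The Results section on COST-FACIT reports that age group, education, employment and residence "were significantly associated with COST-FACIT scores". It gives no result by arm.

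**The concern.** A randomised trial earns its causal claim on an outcome by comparing that outcome between arms. Here the one inferential analysis stated for COST-FACIT makes it the explanatory variable and quality of life the response. It asks whether people with more financial distress have worse quality of life. It does not ask whether navigation changes financial distress. Randomisation plays no part in the answer, and the association is open to confounding by factors such as employment and residence.

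If the section is followed as written, one of the three listed main outcomes yields only observational associations, and the stated purpose words these as an *impact*. A smaller point of method is that ANOVA relates a score to groups. Applying it to two continuous scores means grouping one of them, which discards information, and the article gives no grouping.

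**Working it through.** **1. The two instruments side by side (Data Analysis section).**

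| | FACT-B | COST-FACIT |
|---|---|---|
| Status | Main outcome; primary measure; basis of sample size | Main outcome; no power statement |
| Measured in both arms (Table 2) | Yes | Yes, baseline and 6 months |
| Between-arm comparison stated | Yes | No |
| Time-by-group term stated | Yes | No |
| Inferential analysis stated | Repeated-measures ANOVA by arm | ANOVA of association with quality of life |

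No other section supplies an arm contrast for COST-FACIT. The intention-to-treat sentence covers all quantitative data, but it says who is analysed and in which group. It does not name a contrast.

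**2. Is the missing estimate obtainable, and how precise would it be?** The article gives no COST-FACIT precision or power figure to reproduce.

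Inputs:
- SD 9.85, from the pretest of 30 patients (Data Measurement Instruments and Outcomes).
- 54 completers per arm at 6 months (Study Timeline).
- Two-sided 5% level.
- Correlation between baseline and 6-month scores: not given; 0.6 is assumed.

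Unadjusted 95% CI half-width, with t(0.975, 106 df) = 1.983:
1.983 × 9.85 × √(2/54) = 1.983 × 9.85 × 0.1925 = **3.76 points**.

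Adjusted for baseline, multiply by √(1 − ρ²). At ρ = 0.6 the factor is √(1 − 0.36) = 0.80, and 3.76 × 0.80 = **3.01 points**. As ρ runs from 0 to 0.6, the half-width runs from 3.76 to 3.01.

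The SD comes from only 30 patients, so a range of 8 to 12 is also shown:
- SD 8: 1.983 × 8 × 0.1925 = 3.05 unadjusted; × 0.80 = 2.44.
- SD 12: 1.983 × 12 × 0.1925 = 4.58 unadjusted; × 0.80 = 3.66.

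**3. Detectable difference** (unadjusted, normal approximation, SD 9.85, 54 per arm):
- 80% power: (1.960 + 0.842) × 9.85 × 0.1925 = 5.3 points.
- 90% power: (1.960 + 1.282) × 9.85 × 0.1925 = 6.1 points.

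**4. How many have a 6-month score?** The 164 beside COST-FACIT in Table 2 stands in the enrolment column. The Study Timeline gives 108 completers, so 164 − 108 = 56 did not complete (56/164 = 34%). The figures in steps 2 and 3 describe completers.

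**The case against.** The best reply is that this is a condensed article. Only the primary measure gets a full between-arm model. COST-FACIT and the satisfaction surveys get short sketches, and models for non-primary outcomes may sit in a full protocol or analysis plan that is not shown. Descriptive statistics could be presented by arm. FACT-B is the primary measure, and the stated aim is quality of life and functional outcomes.

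Part of this stands. It limits the point to what the article states, and it keeps financial distress below FACT-B in rank. It does not remove the point, because the article is not silent on COST-FACIT. It fixes an inferential analysis, and that analysis answers a different question. Descriptive statistics by arm would not fill the gap. Among completers, employment is 46.3% in control and 29.63% in intervention, and rural residence is 55.56% and 81.48%. The Results report both factors as associated with COST-FACIT, so a raw 6-month contrast could mislead.

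Four stronger readings are tempting, and the document does not support them:
- *The trial cannot say whether navigation changes financial distress.* It can, since the data are scheduled in both arms at both times. It will not do so under the analysis as written.
- *Financial distress is the leading outcome because it is named first.* List order is not priority, and FACT-B is the primary and powered measure.
- *The Results show that an arm comparison has been abandoned.* That section is one sentence with no time point, and publication of the results is anticipated in December 2026.
- *A specific loss of information from dichotomising can be charged to the plan.* No cut-point or median split is stated, so no such figure applies.

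The word *impact* is also a modest fault, because the same sentence goes on to speak of associations.

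**Conclusion.** The point holds in a limited form. Financial distress is a listed main outcome measured in both arms, and the analyses stated for it contain no randomised comparison. Followed as written, the trial will not estimate the effect of navigation on it. This is an inconsistency between the outcome list and the analysis section. It does not affect the FACT-B analysis and is not a fault in the data collected.

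The forgone estimate would have a 95% CI half-width of about 3.8 points unadjusted, or about 3.0 with baseline adjustment. These figures assume the 30-patient pretest SD of 9.85, 54 completers per arm and, for the second, a correlation of 0.6. They show that the comparison is feasible, not that it is adequately powered. The textual finding depends on none of them. A change should be made, but it ranks below anything that touches the primary measure.

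**What to change.** Add to the Data Analysis section, in substance: *COST-FACIT at 6 months is compared between randomised arms, adjusted for baseline COST-FACIT, and reported as a difference with 95% CI.*

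State how missing 6-month scores are handled. Either fit a likelihood-based model that includes the baseline score, with baseline and 6-month scores as joint outcomes, or use multiple imputation, so that all 164 randomised participants contribute. A regression of the 6-month score on baseline, without imputation, would drop the 56 non-completers. Both methods assume that dropout is explained by the data in the model. Because COST-FACIT has only one follow-up assessment, they will add little precision over the completers' analysis.

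Date the addition and disclose that it was made after data collection ended on September 30, 2025, and after some results by arm had been printed.

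Keep the COST-FACIT and quality-of-life question, but label it exploratory. Use linear regression on the continuous score, adjusted for arm, and replace *impact* with *association*.

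The cost is a few sentences, one secondary model and a missing-data method, with no new data. The drawback is that the comparison is not powered and must be read as a late addition. Removing financial distress from the main outcomes would also make the text consistent, but it would demote an outcome after some results had been reported.

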## Results

### Study Timeline

Data collection took place from January 2 to September 30, 2025. Funding was secured in June 2022; the study has progressed through data validation and cleaning; publication of the results is anticipated in December 2026. A total of 164 participants were recruited at baseline and randomized into either the intervention group (n=82) or the control group (n=82), as shown in Figure 1. At the end of the 6-month follow-up, 108 participants had completed the study (54 in the intervention group and 54 in the control group), resulting in a response rate of 65.85%.

### Sociodemographic Characteristics

In the intervention group (n=54), the largest age group was 40-49 years (17/54, 31.48%), whereas the control group (n=54) was slightly older, with the largest age group being 50-59 years (24/54, 44.44%). Educational attainment was comparable across both groups, with individuals who had completed college, associate, or technical levels comprising 33.33% (18/54) of the intervention group and 37.04% (20/54) in the control group.

Differences were observed in employment and residency. The control group reported a higher employment rate (25/54, 46.3%) than the intervention group (16/54, 29.63%). A higher percentage of the intervention group resided in rural areas (44/54, 81.48%) compared to the control group (30/54, 55.56%).

### Functional Assessment of Cancer Therapy–Breast

At the 6-month follow-up, participants in the intervention group demonstrated higher mean scores across all FACT-B domains than the control group. The intervention group reported higher mean scores (mean 25.6, SD 5.2) on the breast cancer subscale than the control group (mean 24.5, SD 7.1; *P*<.01), indicating improved QOL outcomes.

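### The Results conclude that quality of life improved from 6-month means alone, without baseline, change, time-by-group or FACT-B total results, and the printed figures do not support that conclusion

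*Protocol article*

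**What the plan says.** The Data Analysis section gives the FACT-B its role: "The FACT-B is the primary measure used to evaluate the effectiveness of professional navigation on health-related QOL". What will be compared between arms is "Changes in FACT-B total scores and the scores on its 5 subscales", from baseline (T1) to 3 months (T2) and 6 months (T3). The test is also fixed: "A repeated-measure ANOVA will be used to determine the interaction between time and the treatment group". The same section applies intention to treat to all quantitative data and takes a change of 6 to 7 points on the FACT-B as clinically significant. Sample Size and Power sizes the trial on 7 FACT-B points with an SD of 16.93.

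The Results section on the FACT-B reports: "At the 6-month follow-up, participants in the intervention group demonstrated higher mean scores across all FACT-B domains than the control group". The only numbers follow: "The intervention group reported higher mean scores (mean 25.6, SD 5.2) on the breast cancer subscale", against a control result of "mean 24.5, SD 7.1; *P*<.01), indicating improved QOL outcomes". No test is named.

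On the data behind this, Study Timeline says that "the study has progressed through data validation and cleaning" and that "108 participants had completed the study (54 in the intervention group and 54 in the control group", out of 82 randomised to each arm. It expects the results to be published in December 2026.

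**The concern.** The article states its own standard for effectiveness and then draws an effectiveness conclusion without showing anything that meets it. Improvement, in the plan's terms, is a difference between arms in change from T1. What is shown is a difference in level at T3, in numbers for one subscale only.

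Three consequences follow.

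- A reader cannot set the result against the trial's own 6-to-7-point benchmark, because no FACT-B total is reported.
- The comparison appears to be of completers. About a third of each arm is missing, so the two groups compared are no longer simply the randomised groups, and baseline values are needed to judge them.
- The one P value that carries the conclusion does not match the means and SDs printed beside it.

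At stake is a published statement that navigation improves quality of life, in an article whose Discussion speaks of influencing health policy.

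**Working it through.** **1. Plan and report side by side**

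| Element | Data Analysis section | Results, FACT-B section |
|---|---|---|
| Scores | Total and 5 subscales | Direction for all domains; numbers for 1 subscale; no total |
| Quantity | Change from T1 | Mean at T3 |
| Visits | T1, T2, T3 | T3 |
| Test | Time-by-group interaction | Not named |
| Population | Intention to treat (82 and 82 randomised) | Apparently the 54 and 54 completers |

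**2. Which score is powered.** Sample Size and Power says FACT-B without the word total. Its SD of 16.93 is far above the breast cancer subscale SDs of 5.2 and 7.1, so the 7-point difference cannot sensibly refer to that subscale. The total is the natural reading, but it is an inference.

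**3. The printed P value.** Inputs: 25.6 (SD 5.2) and 24.5 (SD 7.1) from the Results; n = 54 per arm from Study Timeline.

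- Difference = 25.6 - 24.5 = 1.1.
- SE = sqrt((5.2² + 7.1²)/54) = sqrt((27.04 + 50.41)/54) = sqrt(1.434) = 1.20.
- t = 1.1/1.20 = 0.92 on 106 df; two-sided P = .36 (Welch also .36; one-sided .18).
- 95% CI = 1.1 ± 1.98 × 1.20 = -1.3 to 3.5.
- Standardised difference = 1.1/sqrt((27.04 + 50.41)/2) = 1.1/6.22 = 0.18 SD.

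The printed P<.01 is not reproduced. Variations do not rescue it:

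- Rounding most favourable to significance gives P = .31.
- Taking all 82 per arm gives P = .26.
- To reach P<.01 with 54 per arm, the difference would have to be about 3.1 points.
- At a difference of 1.1, it would take about 425 per arm.
- In a baseline-adjusted analysis whose difference stayed at 1.1, it would take a baseline-to-6-month correlation of about 0.94.

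**4. Who is being compared.** Loss is (164 - 108)/164 = 34.1%, or 28 of 82 in each arm. Sociodemographic Characteristics describes 54 per arm. Rural residence is 44/54 (81.48%) against 30/54 (55.56%); chi-square 8.41, P = .004; Fisher P = .007. Employment is 16/54 (29.63%) against 25/54 (46.3%). The same Results section associates residence and employment with financial toxicity scores, so these are not incidental characteristics.

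**5. Can the planned test be computed from what is shown?** No. It needs T1 values or change scores by arm, and neither is given. The plan also requires the FACT-B at T2, while Table 2 schedules it only at T1 and T3. With two visits the time-by-group interaction reduces to the between-arm difference in change from T1 to T3; the three-visit model cannot be fitted to data collected under Table 2.

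**The case against.** The strongest reply is that this is a protocol article. The full results are due in December 2026, the abstract reports no effect, and totals, baseline means and intervals may be left to the later paper. That stands as regards omission: leaving results out of a protocol article is no fault. It does not cover a conclusion that is stated here, without a preliminary label and with a P value its own figures contradict.

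Four stronger readings are tempting, and the documents do not support them.

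- *A comparison at 6 months only is invalid.* Between randomised arms it is not. Chance baseline variation is already contained in its standard error, and baseline adjustment mainly adds precision. For the same reason, the .36 above must not be read as the probability that a chance baseline gap explains the result; it is the ordinary P value of the 6-month difference. The real threat is the 34% loss together with the rural imbalance.
- *A different analysis replaced the planned one.* The test behind P<.01 is unnamed. It cannot be an independent-groups t test on the printed figures with 54 or 82 per arm, but it could be an unreported model, even the planned one, or an error.
- *The arms were compared before the planned model was run.* This would rest on the future tense in Data Analysis. Tense is unreliable here: the Discussion says the trial is still recruiting, although data collection ended on September 30, 2025.
- *Analysis choices were left open until results were known.* A statistical analysis plan may exist that fixed them, so this cannot be held against the article.

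The subscale is also one of the planned scores, so reporting it is not in itself a departure from the plan.

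**Conclusion.** The conclusion of improved quality of life is not supported by what the article reports. The only numeric comparison is 1.1 points on one of six FACT-B scores, 95% CI about -1.3 to 3.5, P about .36. That is compatible with no difference and cannot be measured against the 7-point benchmark. The planned evidence (change from T1, time-by-group interaction and FACT-B total, under intention to treat) is absent.

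This rests on three assumptions: that the 6-month figures come from the 54 completers per arm (with 82 per arm, P is .26 and the conclusion is the same), that the dispersion figures are standard deviations as labelled, and that the total is the powered score. It does not show that the intervention is ineffective, nor that the planned analysis was skipped or would fail.

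**What to change.** In the Results section on the FACT-B:

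- Delete the closing clause that interprets the difference as improved quality of life.
- Label the 6-month means by arm as preliminary and descriptive, with the number analysed per arm.
- Name the test behind P<.01 and report its estimate, or correct the P value.

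Base any effectiveness statement, here or in the later results paper, on the planned between-arm contrast in FACT-B total change from T1 to T3. Give its 95% CI and the T1 means by arm, in the intention-to-treat population, and say how the 56 participants without a 6-month assessment were handled.

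Reconcile the Data Analysis section, which uses the FACT-B at T2, with Table 2, which schedules none there. If no T2 scores were collected, state the analysis as change from T1 to T3.

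The cost is wording plus one model on existing data, since Table 2 schedules the FACT-B at both T1 and T3. The downside for the sponsor is that the stated result may become less favourable. The contrast need not be published in the protocol article; removing the claim is enough until the results paper.

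### The P<.01 printed for the 6-month breast cancer subscale does not follow from the means, SDs and arm sizes given (they give P=.36), so the benefit wording that rests on it is unsupported as written

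*Protocol article*

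**What the plan says.** The Results section headed Functional Assessment of Cancer Therapy–Breast first states, without figures, that the intervention arm had higher means on every FACT-B domain at 6 months. It then gives figures for one domain: "The intervention group reported higher mean scores (mean 25.6, SD 5.2) on the breast cancer subscale than the control group (mean 24.5, SD 7.1". P<.01 follows in the same parenthesis, and the sentence closes with "indicating improved QOL outcomes". No test, model or adjustment is named, and no baseline values are shown.

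The number analysed is not stated there. The Study Timeline section reports 164 randomized (82 per arm) and that "108 participants had completed the study (54 in the intervention group and 54 in the control group".

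The Data Analysis section names the FACT-B as the primary measure. It plans to compare "Changes in FACT-B total scores and the scores on its 5 subscales" from baseline between arms, using a repeated-measures ANOVA to test the time-by-group interaction. The Sample Size and Power section bases the trial on a 7-point FACT-B difference at a two-tailed 5% level.

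**The concern.** The sentence sets two 6-month means side by side, attaches a P value to them, and draws a conclusion about benefit. A reader can only take P<.01 as the test of those two means. A gap of 1.1 points against SDs of 5.2 and 7.1 is small for arms of this size, so such a low P value is not plausible on its face.

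No other between-arm effectiveness comparison in the article has both figures and a P value. The remaining FACT-B domains get only a statement of direction, and the COST-FACIT results concern associations with sociodemographic factors, not arms. The claim of improved quality of life therefore rests on this one figure. The article expects results to be published in December 2026 and hopes to inform health policy, so an uncorrected figure could carry forward.

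**Working it through.** **Inputs**
- Intervention: mean 25.6, SD 5.2; control: mean 24.5, SD 7.1 (Results, FACT-B section).
- n = 54 per arm (Study Timeline), with 82 per arm randomized as a sensitivity check.
- Two-sided test (Sample Size and Power).
- Figure to reproduce: P<.01.

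**Comparison as worded**
- Difference = 25.6 − 24.5 = 1.1.
- SE = √(5.2²/54 + 7.1²/54) = √(77.45/54) = √1.434 = 1.198.
- t = 1.1/1.198 = 0.918 on 106 df.
- Two-sided P = .360 (Welch .361).
- 95% CI = 1.1 ± 1.98 × 1.198, about −1.3 to 3.5.

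The printed P<.01 is not reproduced.

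**Attempts to recover P<.01 from the same means and SDs**

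| Variant | P |
|---|---|
| One-sided, n=54 per arm | .18 |
| All randomized, n=82 per arm: SE = √(77.45/82) = 0.972, t = 1.13 | .26 |
| Most favourable rounding, n=54 per arm (25.65 vs 24.45; SDs 5.15, 7.05): SE = √(76.225/54) = 1.188, t = 1.01 | .31 |
| Most favourable rounding, n=82 per arm | .22 |

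To reach P<.01 with these means and SDs would take 427 per arm, about five times the 82 randomized. At 54 per arm it would take a difference of 2.62 × 1.198 = 3.1 points.

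**Baseline adjustment of the same 1.1-point difference** (correlation ρ between baseline and 6 months is assumed, as the article gives none; SE becomes 1.198 × √(1 − ρ²))
- ρ = 0.5: P = .29
- ρ = 0.7: P = .20
- ρ = 0.8: P = .13
- P = .01 is reached only at ρ of about 0.94.

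**Could a change-from-baseline analysis give P<.01?** (ρ assumed; SDs assumed equal over time; SE becomes 1.198 × √(2(1 − ρ)))
- ρ = 0.7: SE = 1.198 × √0.6 = 0.93. P = .01 needs a difference in change of 2.62 × 0.93 = 2.4 points, so the control arm would have had to start about 2.4 − 1.1 = 1.3 points higher.
- ρ = 0.5: SE = 1.198. P = .01 needs 3.1 points, so a baseline gap of about 2.0 points.

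This route is possible, but it rests on baseline values the article does not print.

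**The case against.** The strongest reply is that the plan's effectiveness test is not a comparison of 6-month means. It is the time-by-group interaction on repeated measures. Baseline FACT-B scores are not reported, and the completers differ between arms (rural residence 81.48% vs 55.56%, employment 29.63% vs 46.3%), so some baseline imbalance in FACT-B is conceivable. On the assumptions above, a control arm starting 1.3 to 2.0 points higher would be enough for P=.01. This stands. A reader might infer from P=.36 that the planned analysis is null or that the intervention has no effect, and the printed figures do not support that. They show only that P<.01 is not the test of the two means it accompanies. The reply does not rescue the sentence, which names no such model and gives no changes or baseline values.

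A second inference is that the trial has no primary outcome and that the subscale was picked from many tests. The article does list several main outcomes without ranking them ("The main outcomes are financial distress; QOL, such as physical, social, emotional, and functional well-being; and satisfaction with navigation and interpersonal relationships"). But Data Analysis names the FACT-B as the primary measure, and the 7-point planning difference suggests its total score. The plan describes an interaction test across time, not a separate test at each visit, and Table 2 schedules no FACT-B at 3 months. Multiplicity rules are commonly left to an analysis plan, which is not shown here. Only one test result is printed, so selection among scores would be conjecture.

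It is also fair to say that the abstract's conclusion speaks only of an aim to demonstrate effectiveness. The benefit wording is confined to the Results sentence.

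**Conclusion.** The point holds for the printed result. The means, SDs and completer numbers give a difference of 1.1 (95% CI about −1.3 to 3.5) and P=.36. Neither rounding, nor Welch's test, nor a one-sided test, nor the full randomized number brings P near .01. At least one of the P value, the means or SDs, and the contrast is misstated. If the P value belongs to the planned interaction test, it is attached to the wrong figures.

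The main assumption is that the 54 completers per arm supplied the subscale scores; with 82 per arm the conclusion is the same (P=.26). What the planned model would show cannot be settled from the article. Until that is reported, the inference of improved quality of life has no support in the figures given. The correction is necessary because no other quantified between-arm effectiveness result stands beside this one.

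**What to change.** 1. Re-run the comparison and name the contrast, the model, the time points entered and the number analysed per arm.
2. Replace P<.01 with the between-arm difference, its 95% CI and the P value from the planned model, and print the baseline values or changes it uses. If the means or SDs are the error, correct those.
3. Remove "indicating improved QOL outcomes" unless that test supports it.
4. Report the FACT-B total, which the 7-point sample-size basis suggests, ahead of any subscale.
5. If the total at 6 months is now named as the score that carries the conclusion, disclose that this was fixed after data collection and after an outcome result had been printed. Otherwise a late choice would look prespecified.

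The cost is one re-analysis of data already collected and cleaned, a few lines of text, and possibly the loss of a favourable-looking P value.
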